### Interventions

The acute aerobic exercise intervention will consist of one 20 min cycling interval preceded by a 5 min warm-up and followed by a 5 min cool-down (total duration of 30 min) and will be performed on a stationary electromagnetically braked cycle ergometer (Schoberer Rad Messtechnik, Jülich, Germany). Self-selected exercise intensity will be guided to moderate intensity by using Borg Ratings of Perceived Exertion (RPE) Scale with a target RPE of 13–15 (somewhat hard/hard).^45^ Borg RPE and self-rated pain on Visual Analogue Scale (VAS) (0–100 mm) will be recorded every 5 min during the exercise session. Power output, cadence and heart rate will be recorded at 2 Hz. Participants will be able to freely regulate cadence and resistance to maintain the target RPE of 13–15, by means of a 14-increment mechanical gear shifter located on the handlebars. The ergometer is equipped with an upright handlebar, flat pedals and a wide-padded saddle with an extra gel cover to minimise sitting discomfort.

Participants allocated to the control groups will rest for the equivalent period of 30 min in a self-selected comfortable resting position accompanied by staff.

### Outcome measures

The primary outcomes (detailed in table 1) are kinematic measures of human movement and muscle activity that will be measured while participants are walking using the following three gait conditions: (1) self-selected habitual gait speed, (2) brisk gait speed and (3) self-selected habitual gait speed with a concurrent cognitive task. Our primary kinematic outcomes are gait speed, step frequency, stride length, lumbar rotation and gait stability, while primary outcomes for the muscle activity domain will be mean normalised electromyography (EMG) amplitude averaged over aggregated gait cycles.

**Table 1 T1:** Outcomes and assessments

			Baseline	Intervention	Follow-up
Baseline measures	Variable or assessment	Data Source			
Participant characteristics	Age, sex, body mass index (weight, height), educational level, work status, physical activity.	SAQ+PT	X		
Pain catastrophising*	Pain Catastrophizing Scale (PCS)	SAQ	X		
Effects on everyday life*	Multidimensional Pain Inventory (MPI)	SAQ	X		
Primary outcome measures					
**Gait kinematics** Gait speed (m/s) Step frequency (steps/min) Stride length (cm) Lumbar rotation (°) Lateral step variability (three consecutive steps, the perpendicular deviation of the middle foot placement from the line connecting the first and the third step) **Back and neck muscle activity** Normalised mean muscle activity of all completed gait cycles per trial Back and neck normalised muscle activity at each 10 percentile of gait cycle	Gait kinematics with IMU-based sensors and wireless surface EMG, aggregated from minimum 50 gait cycles Self-selected habitual gait speed Brisk gait speed† Self-selected habitual gait speed with concurrent cognitive task (1-back test)†	PT	X		X
Secondary outcome measures					
**Variability of gait kinematics** Gait speed (m/s) Step frequency (steps/min) Stride length (cm) Lumbar rotation (°) Lateral step variability **Variability of muscle activity** Normalised mean per trial Balance of left/right at each 10 percentile of gait cycle Back and neck normalised during stance and swing phase Number of muscle activity spikes (˃100% normalised per complete gait cycle)	Non-linear analysis of gait kinematics with IMU-based sensors and wireless surface EMG, aggregated from minimum 50 gait cycles Self-selected habitual gait speed Brisk gait speed† Self-selected habitual gait speed with concurrent cognitive task (1-back test)†	PT	X		X
Pain intensity*	VAS (0–100)	SAQ	X	X	X

Data source: self-administered questionnaire (SAQ), physical testing (PT).

*Only measured in patients with chronic musculoskeletal pain.

†Brisk gait speed and self-selected gait speed with the 1-back test will be performed in random order.

EMG, electromyography; IMU, inertial monitoring unit; RPE, rating of perceived exertion (every 5 min during the intervention); VAS, Visual Analogue Scale (administered after every gait test).

Our secondary outcome measures are variability of gait kinematics and muscle activity and self-rated current pain intensity using a horizontal 100 mm line VAS with the statement ‘no pain at all’ at the extreme left and ‘the worst possible pain’ at the extreme right (chronic pain sample only).^46 47^

### Trial procedure, instruments and data collection

The entire trial procedure at the laboratory is expected to take approximately 3 hours and will be supervised by two researchers. On arrival at the laboratory, eligibility screening, presentation of the study procedures and collection of informed consent (online supplemental appendix 2) will be performed. Participants will complete the following questionnaires before commencing any testing: (1) participant characteristics (age, sex, educational level, occupational status, pain locations, pain duration) including two validated items with questions about physical activity.^48^ Participants with chronic musculoskeletal pain will also complete the following two questionnaires relating to pain experiences: (2) the Pain Catastrophizing Scale,^49^ which contains 13 items regarding participants’ thoughts and feelings associated with pain, with a total score ranging from 0 to 52, with higher scores representing higher pain catastrophising and (3) the West Haven-Yale Multidimensional Pain Inventory, which is a questionnaire that measures the psychosocial, cognitive and behavioural effects of chronic pain.^50–53^

10.1136/bmjopen-2022-069747.supp2Supplementary data

A researcher will then record participant body height using a stadiometer (Harpenden Stadiometer, Holtain Limited, Crosswell, UK) and body weight using a weighing scale (Midrics, Sartorius AG, Goettingen, Germany). Participants will be introduced to the 1-back test^54^ and listen to a 30 s practice sequence, then two 30 s 1-back baseline tests will be recorded with participants in a seated position. The 1-back test will be performed with a pair of minimally intrusive wireless handsfree on-ear headphones connected via Bluetooth to a PC using Audacity Software V.2.3.0. Participants will listen to an audio file consisting of a randomised number sequence and will be instructed to respond as quickly and accurately as possible to audio prompts, repeating the digit before the last one in the consecutive sequence during the entire 1-back walking trial. All responses will be recorded.

After this, seven wireless inertial monitoring unit sensors (OPAL, APDM, Oregon, USA) incorporating a three-axis gyroscope, accelerometer and magnetometer will be applied on participants’ limbs using elastic straps as specified in figure 2. Gait kinematics will be streamed and logged wirelessly from each sensor at 128 Hz during all trials and will be automatically processed via Moveo Explorer software to extract gait variables specified as primary or secondary outcomes according to table 1.^55^ Participants will be given standardised instructions prior to starting each gait trial in order to comply with the initial calibration procedure described by the manufacturer.

**Figure 2 F2:**
[figure not shown]
Inertial monitoring unit sensor placement on the forehead, sternum, lumbar spine, wrists and feet. Adapted with permission by APDM.

Wireless EMG sensors (Delsys Trigno, Delsys, Boston, Massachusetts, USA) will be positioned according to anatomical landmarks detailed in figure 3, as per surface EMG for the non-invasive assessment of muscles guidelines^56 57^ and data will be recorded at 1111 Hz. Skin will be shaved and cleansed with a chlorhexidine digluconate ethanol cutaneous solution (Klorhexidinsprit 5 mg/mL, Fresenius Kabi AB, Uppsala, Sweden). To obtain normalised (reference) muscle activity, each participant will perform four standardised submaximal standing trunk flexion (hip flexion to 45° from neutral standing position) muscle contraction tests, interspersed by a 60 s rest. EMG sensors will be removed after baseline measurements and reapplied prior to the follow-up walking trials. Before removal, sensor positions will be marked with a marker pen to facilitate accurate reapplication.

**Figure 3 F3:**
[figure not shown]
Overview wireless electrode placement for surface EMG recording of the trunk and neck musculature according to surface electromyography for the non-invasive assessment of muscles guidelines (http://www.seniam.org/).

All gait trials will be performed indoors in a continuous fashion on a 15 m standardised walkway with tape markings on the floor indicating starting and 180° turning points. Trials will have a minimum duration of 2 min and finish when participants cross the start line with a time exceeding 2 min. Participants will initially perform a familiarisation trial at a self-selected habitual speed followed by a short rest if needed, to avoid any accumulated pain or fatigue. After this, participants will proceed to walk the 15 m walkway under the three different conditions described above: (1) an initial self-selected habitual gait speed, (2) a brisk gait speed and (3) a self-selected habitual gait speed with a concurrent cognitive task (1-back test). The order of performance of the brisk and 1-back walking conditions (2 or 3) will be randomised and the allocation will be kept concealed from the participants until the initial condition with self-selected habitual gait speed has been performed. For the brisk walking condition, participants will be instructed to walk faster than they habitually do, as they imagine themselves doing when slightly late for a bus they want to catch. The self-rated pain intensity (VAS) of participants with chronic musculoskeletal pain will be recorded after each walk trial. The risk of complications due to measurements or interventions is considered to be low, but any adverse or serious adverse events will be logged and reported as well as covered by laboratory insurance.

### Data management

Participant questionnaires will be checked for completeness and congruity before data is entered into the database. Data will be stored on secure university servers and in locked cabinets only available to the research team. Gait kinematics will be aggregated for all valid gait cycles of each gait condition. For each individual, a minimum of 50 gait cycles will be used and aggregated prior to analysis.^58^ Back and neck muscle activity (root mean square (RMS)) synchronised to gait cycles and aggregated from each gait condition will be normalised as percentage RMS against reference contractions.

### Statistical analysis

Participant characteristics will be reported using descriptive statistics. The statistical analyses will be performed on an intention-to-treat basis and potential differences between the intervention groups and the control groups will be analysed. Analysis will primarily be conducted with variance analysis with respect to both data quality and distribution (data assumptions) and with the addition of repeated measurements where applicable. Log transformations of data will be made as appropriate. Data will be presented with means and variances. To explore the magnitude of the effect of interventions, effect sizes will be calculated.^59^ Lastly, non-linear analysis using Gait Evaluation Differential Entropy Method^60^ will be used to assess variability of gait kinematic and muscular activity.^60–62^

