#### Randomisation, allocation concealment and blinding

Participants will be randomly assigned to either the intervention or control group at a 1:1 allocation ratio, using stratified block randomisation with a fixed block size of six within the chronic musculoskeletal pain and no chronic pain strata. Allocation information is kept in opaque sealed envelopes and will not be disclosed to participants or researchers until all baseline walk trials are completed. All data collection will be automated in preprogrammed sequences and participant instructions read verbatim to minimise any investigator bias influencing participants’ behaviour. Participants will not be informed of the hypotheses of the study, and the researcher performing the data analyses will be blinded to group allocation.

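### For exercise versus rest, the planned repeated-measures variance analysis is less precise than adjusting for the pre-allocation baseline, and naming that adjustment costs almost nothing

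*Protocol article*

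**What the plan says.** All of the following is in the protocol article.

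- Statistical analysis names one family of methods for the main outcomes: "Analysis will primarily be conducted with variance analysis", and then "with the addition of repeated measurements where applicable". No factors, covariates or missing-data rule are given.
- The same section states: "The statistical analyses will be performed on an intention-to-treat basis".
- Under Randomisation, allocation concealment and blinding, allocation "will not be disclosed to participants or researchers until all baseline walk trials are completed". Baseline is therefore a genuine pre-allocation covariate.
- Under Outcome measures, the primary outcomes are "measured while participants are walking using the following three gait conditions", and Table 1 marks all of them at baseline and at follow-up. This gives 3 × 2 = 6 cells per participant and outcome.
- In the procedure section, after Figure 2: "EMG sensors will be removed after baseline measurements and reapplied prior to the follow-up walking trials".

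**The concern.** With one baseline and one follow-up, the arm-by-time interaction in a repeated-measures analysis of variance is the difference between arms in mean change. Subtracting baseline in full is the best use of it only when the correlation is perfect. At lower correlation the change score carries the noise of both measurements, while adjustment takes out only the part of baseline that predicts follow-up.

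The contrast at stake is exercise versus rest, which carries the main aim. It rests on 20 against 20 within each sample. The only power statement, under Trial design, is for patients against reference participants, 40 against 40. Precision for the randomised contrast is therefore worth having where it is free.

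**Working it through.** **The plan's own figure.** The stated total is 80 for 80% power, two-sided α of 0.05 and a 25% difference between patients and reference participants. It can be neither confirmed nor refuted, because no SD is given. Solving backwards by the normal approximation, d = (1.960 + 0.842) × √(2/40) = 0.627, so a coefficient of variation of 0.25/0.627 ≈ 0.40 would reproduce it. This figure concerns the non-randomised contrast and says nothing about the size of an exercise effect.

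**Inputs for the check.** 20 per arm within each sample (Trial design). One baseline and one follow-up value per condition (Table 1). The correlation ρ is not given, so it is assumed and shown over a range. Equal variance at both times is assumed. The formulas hold for one walking condition, or for the mean over conditions with ρ taken for that mean.

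**Formulas**, in units of the variance for follow-up alone:
- change score (the arm-by-time test): 2(1−ρ)
- baseline-adjusted: 1−ρ² = (1−ρ)(1+ρ)
- ratio, adjusted to change score: (1+ρ)/2
- smallest difference detectable with 80% power, in SD units: (1.960 + 0.842) × √(2v/20), with v the variance above

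| Assumed ρ | Change score | Adjusted | Ratio | SE falls by | Detectable difference, change score → adjusted |
|---|---|---|---|---|---|
| 0.3 | 1.40 | 0.91 | 0.65 | 19.4% | 1.048 → 0.845 |
| 0.5 | 1.00 | 0.75 | 0.75 | 13.4% | 0.886 → 0.767 |
| 0.7 | 0.60 | 0.51 | 0.85 | 7.8% | 0.686 → 0.633 |
| 0.9 | 0.20 | 0.19 | 0.95 | 2.5% | 0.396 → 0.386 |

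**As sample size.** The inverse of the ratio gives the equivalent gain in participants: 1/0.75 = 1.33, 1/0.85 = 1.18 and 1/0.95 = 1.05.

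**As power.** Where the change-score test has a nominal 80%, the normal approximation gives the adjusted analysis 90%, 86% and 82% at ρ of 0.5, 0.7 and 0.9. A simulation with 20 per arm and 4,000 runs gave 79% to 88%, 77% to 83%, and 79% to 79%. At ρ = 0.9 the gain is therefore lost in simulation error and the spent degree of freedom.

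**Where ρ is likely to lie.** Removing and replacing the EMG sensors adds error between the two sessions and lowers ρ, so a moderate value is plausible for muscle activity. A value near 0.9 is possible for gait speed or step frequency. Both are judgements; the documents have no figure. Below ρ = 0.5 the change score has a larger variance than follow-up alone (2(1−ρ) > 1), so the named method could do worse than ignoring baseline.

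**The case against.** The strongest reply is that the article fixes very little. Variance analysis can include a covariate, the words on repeated measurements are conditional, and covariates and missing-data handling are what a condensed article leaves to the full plan. This stands in part: the text is neither wrong nor contradictory, and a missing covariate list is no finding. But the article does name a method, and in its ordinary reading that method is the less efficient one for this design.

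A reader might infer three stronger points, which the documents do not support.

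- *That intention to treat requires a mixed model.* It requires analysis as randomised. Missing data can be handled in several ways.
- *That the plan will lose randomised participants.* Complete-case deletion is not stated. If each of six cells were missing independently in 1%, 2% or 5% of participants, 75, 71 or 59 of 80 would be complete ((1−p)^6), but these rates and the independence are assumptions. Failures that cluster within a person would remove fewer people. The whole procedure "is expected to take approximately 3 hours and will be supervised by two researchers", so few losses are likely.
- *That the gain is as large as against follow-up alone* (1−ρ² = 0.75, 0.51 and 0.19 at ρ of 0.5, 0.7 and 0.9). The plan adds repeated measurements to outcomes taken at both times, so the change score is the fair comparator. Nor can the trial's power for exercise versus rest be stated: an effect size of 0.63 can only be back-solved from the patient-versus-reference calculation.

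A further objection stands in full. A model of follow-up values alone does not estimate the baseline difference between patients and reference participants, which the Introduction hypothesises, together with its growth with task difficulty, and which Trial design powers. Adjustment must not replace that analysis.

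**Conclusion.** The point holds as an improvement to the named method, limited to exercise versus rest and its interaction with sample. Adjusting for baseline multiplies the variance of the arm-by-time estimate by (1+ρ)/2. That is a reduction of 25% at ρ = 0.5, 15% at 0.7 and 5% at 0.9, assuming equal variances at the two times. The gain is worth having at moderate ρ and negligible near 0.9. Because no ρ is reported, the size for any one outcome is unknown.

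Keeping participants with some missing conditions is a secondary benefit. It serves the stated intention-to-treat basis better than a complete-case repeated-measures analysis would, but the documents give no missing-data rate from which to size it.

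**What to change.** In Statistical analysis, state that exercise versus rest, and its interaction with sample, will be analysed with a linear mixed model of the follow-up values over the three walking conditions. Include arm, sample, condition and their interactions as fixed effects, the same-condition baseline as covariate, and a term for correlation within participant. Fit it to all available data, state the missing-data assumption, and report the adjusted difference with its 95% CI.

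Keep a separate analysis of the baseline values for the patient-versus-reference difference and its change with task difficulty. The sample term in the adjusted model should not be read as that difference.

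The model has limits that should be acknowledged. A participant with no follow-up walk contributes nothing, and a missing baseline drops that condition's follow-up value.

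The cost is a change of wording and about one degree of freedom per covariate. No new data and no change to the trial procedure are needed.

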### Ethics and dissemination

The study has been approved by the Regional Ethics Review Board in Uppsala, Sweden (#2018/307). Findings will be disseminated via conference presentations, publications in peer-reviewed journals and engagement with patient support groups and clinicians.

### Patient and public involvement

The burden of the study procedures has been assessed by patients during preliminary pilot work, primarily to assess the following areas: the feasibility of the cycling exercise intervention, the baseline questionnaires and the instrumentation to capture gait kinematics and EMG data. Study participants will be invited to a briefing where the results of the study will be presented. In addition, study participants will be given a summary of the results written in Swedish. Results will be presented at the annual meeting of the Swedish National Registry for Chronic Pain Rehabilitation where patient groups are represented.

## Discussion

To our knowledge, the current study is the first RCT to investigate the acute effect of aerobic exercise on gait kinematics and muscle activity in participants with chronic musculoskeletal pain compared with reference participants from a perspective of exercise as active inference. Our two-sample two-armed parallel design allows for a cross comparison of effects in patients with chronic musculoskeletal pain and healthy participants that will follow the same study protocol and will contribute to our understanding of how chronic musculoskeletal pain manifests on measures of human motor behaviour and how exercise can influence this in a rehabilitation setting. Knowledge of how gait kinematics and back and neck muscular activity may change during different gait conditions and from aerobic exercise may contribute to the understanding of how exercise therapy influences our generative models in the process attenuates allostatic load through active inference. The use of modern, miniaturised and completely wireless sensors during overground walking replicates real-world conditions, hence strengthening the ecological validity of our results. Objective measurements of movement and muscular activity during diverse walking conditions have been chosen as primary outcomes since such a methodology can both uniquely and sensitively show and quantify deviating activation patterns as validly reflected in everyday functional movements and commonly performed physical activities.

Selection bias is difficult to completely overcome in exercise intervention studies as volunteering participants will likely be positively biased towards exercise in general and motivation to participate in an exercise intervention is also likely influenced by the severity of symptoms experienced when asked to volunteer for the study. We will compare and validate our sample baseline characteristics with a new nationwide large database including 60 000 patients with chronic pain.^63^

Concerning our reference participants without chronic musculoskeletal pain, we aim to create a sample that is sex and age matched with our chronic musculoskeletal pain sample and will serve as a reference sample for all our outcomes.

Viewing this exercise intervention as active inference will hopefully add knowledge on how acute movement through exercise may promote an individual’s predictions about their body and their world by creating a platform for belief updating. Our use of a cycling modality with a rather different muscle recruitment and joint loading pattern compared with walking may be beneficial, especially since stationary cycling may be more palatable to participants than running at the same intensity as it may lead to an undesired level of fatigue, fear or increased pain.

In addition, the aerobic exercise intervention in the current study reflects recommendations in exercise guidelines and allows an easy progression of rehabilitation in terms of both intensity and duration.^64^ Since a bicycle can be used for therapy, recreation and transportation, there are opportunities for healthcare professionals to facilitate changes in lifestyle that have the potential to mitigate morbidity and function in patients with chronic pain,^65^ simultaneously reducing the risks and impact of common comorbidities.

With the foundation of this project being objective measures of overground walking, it adheres well to the Initiative on Methods, Measurement and Pain Assessment in Clinical Trials, which recommends that all chronic pain trials should include measures of physical functioning.^47^ This project is expected to result in increased knowledge of how acute exercise affects subsequent functional tasks, here measured during different walking conditions.

Our proposed project will deepen our understanding on the topic of alterations in functional movement in chronic musculoskeletal pain conditions. Results from the current study may help us reach a better understanding of how acute aerobic exercise acts as active inference to attenuate chronic pain by facilitating allostasis. This knowledge will help us formulate better questions as to how generative models in chronic pain conditions are formed, maintained and updated through movement, or lack thereof.
